#### 2.4.4. Self-Reported Physical Fitness

The self-reported physical fitness of children (S5) and parents (S6) will be registered using The International Fitness Scale (IFIS), previously validated [44,45], before and after the intervention. This scale evaluates both overall physical condition as well as each one of its primary components specifically: cardiorespiratory fitness, muscular strength, speed-agility and flexibility.

#### 2.4.5. Physical Activity and Screen Time

Physical activity and screen time will be recorded by means of a self-report by the schoolchildren (S3) and observation of the parents using a built-in questionnaire (S4) from the one used in the “Previene” [Prevent] study in Granada [10]. Information will be collected on the amount of physical activity and screen time (TV, computer, video games…) of schoolchildren both before and after the intervention. In addition, the knowledge, attitudes and beliefs about physical activity, sports and sedentary lifestyle presented by both students and families will be evaluated.

#### 2.4.6. Diet

The daily/weekly consumption of processed baked goods, fried foods, snacks, sugary soft drinks, fruits, vegetables, packaged juices, sandwiches, dairy products, carbohydrates, meat, cold cuts, fish, and vegetables, among others, will be recorded through questionnaires [10] applied to schoolchildren (S2) and family members (S4) both before and after the intervention. In addition, the knowledge/beliefs about food and diet of schoolchildren and relatives, and the use of the school canteen and its evaluation [10] will be assessed. Schoolchildren will answer questions about all of these variables about themselves, and parents will answer both about themselves and about their children.

#### 2.4.7. Sleep, Overall Health, Feelings and Emotions

Schoolchildren’s daily hours of sleep, both for Monday to Friday as well as for weekends, will be recorded through questionnaires (S3 and S4) adapted from those used in the “Previene” [Prevent] study in Granada [10]. Parents will be asked about their children before and after the intervention. Parents will have to register the time their children normally go to bed and get up. Furthermore, the general health status, feelings and emotions of the students will be recorded using a specific questionnaire (S3) also adapted from the “Previene” [Prevent] study [10] applied before and after the intervention.

#### 2.4.8. Health Resources

Health resources will be evaluated using the Photovoice qualitative technique [46]. This technique will consist of taking two photographs, one of a resource that encourages healthy eating and the other from a resource that encourages healthy physical activity. Once each family identifies two health resources, the students will return to work on it in the classroom, which means that this activity will involves two sessions in the classroom and at least one with the family. This technique will be used for a dual purpose: (1) to identify the main health resources/assets related to physical activity and diet available to families in the environment of each school; (2) for educational purposes, as this technique will be part of the activities of the intervention, with which it is intended that both schoolchildren and family members identify, become aware of and promote the use of previously identified resources/assets.

#### 2.4.9. Breastfeeding, Childbirth Type and Birth Weight

The characteristics of breast milk intake, type of delivery and birth weight will be recorded after the intervention using a questionnaire for parents (S7), which has been created by the research team based on the information from the scientific literature determined as important about these variables related to childhood obesity [47,48,49,50,51].

#### 2.4.10. Participant Satisfaction/Reaction and Adherence to the Intervention

Once the intervention has been carried out, the participants will be asked about their perception of the program, the main health resources that have been discovered or identified, the strengths and weaknesses of the intervention and any aspects to be improved. The research team will record the answers to these questions to assess the adherence of the participants to the intervention, including children´s adherence, caregivers´ adherence and teachers’ adherence.

These aspects will be studied using two different activities. First, a qualitative technique called “World Cafe” [52] which will consist of gathering a sample of the participating agents (teachers, management teams, parents and schoolchildren) and dividing them into three different groups: (1) teachers and management team, (2) parents, and (3) schoolchildren. Each of the groups will be accompanied by someone from the research team, who will act as a moderator of the table, guiding the conversation through a script of semi-structured questions.

There will be 3 rounds and two changes. Each round will consist of having a conversation between the members of each group about the questions of the semi-structured script. Once all questions in the first-round semi-structured question script are completed, there will be a change. This change will consist in that a member of group 1 will go to group 2, a member of group 2 to group 3 and a member of group 3 to group 1. In this way all groups will have a new member of another group, and it will start a new round following the script of semi-structured questions. Once this round is completed there will be another change, but this time a member of group 1 will go to group 3, a member of group 2 to group 1, and a member of group 3 to group 2, to get each group to have at least one member from each one of the 3 groups, to achieve a multi-group exchange of ideas. Then the last round will begin again following the semi-structured question script, and once it is finished, the main ideas that have emerged from the conversation will be shared. A member of the research team, who will act as moderator of the session, will be in charge of making the decision of when to change rounds and of making the changes.

The aim of this technique will be to know the satisfaction of the participants with respect to the intervention, and also to assess the adherence to the intervention. It will be intended to know if the intervention has achieved real change in the home of the schoolchildren regarding better eating habits, increased levels of physical activity, reduction of sedentary lifestyle and sleep improvement (children´s adherence and caregivers’ adherence), and also to know how the program has gone in the schools (teachers´ adherence).

Qualitative methodology will be used for the analysis of the World Cafe interviews. A content analysis will be carried out on all the information obtained. Both the verbal information (of which an exhaustive transcription will be made), the reports of the table coordinators, the photographic images, as well as the written and iconographic material generated. The development of the sessions, the moment, context and origin of the ideas that arise will always be taken into account. When considering the World Cafe as a semi-structured group interview technique, opinions on development and general effectiveness, the health assets that have been identified, the main strengths and the elements that should be improved in the program will be studied, but within a flexible framework in which all emerging elements will be considered.

Secondly, in addition to the World Cafe, in order to know the satisfaction/reaction and adherence to the intervention of teachers and management teams, a questionnaire will be administered to teachers (S9) and management teams (S8) participating in the study. They will be asked about the development/implementation of the program (whether they carried it out or not, time spent in developing it, dynamics, etc.), as well as if they have modified or supplemented it, and any possible proposals for improvement. These questionnaires will be designed by the research team of this study.

Table 3 lists all the measurements that will be collected, the tools with which they will be measured, and when they will be measured.

### 2.5. Statistical Analysis

A descriptive analysis of the main outcome variables will be carried out with measures of centrality, dispersion and 95% confidence intervals (CI), and percentages or prevalence for the categorical variables. Chi square tests will be used for categorical variables and *t*-test or ANOVA for continuous variables, which will be used for comparisons of percentages or means, respectively, when they have a normal distribution. The effectiveness will be studied by comparing the changes in the groups. Simple and multiple linear regressions and/or logistic regressions with the respective odds ratios (OR) and the 95% CI will be applied as an association measure. The grouping term will be modeled in the analysis to adjust the effect of the intraclass correlation and a multilevel test will be conducted. For this, several levels of grouping will be established. The first level will be constituted by the geographical areas of study, the second by the municipality, the third level of grouping will be the school center and the line or classroom, and the fourth and last will be given by the intervention (control and experimental group).

For the analysis of longitudinal data, MANOVA of maximum likelihood and least squares will be used under conditions of normality of the data (assuming that large sample sizes will be obtained). If the data are not normal, generalized linear models (GLM) will be used. As a strategy for the analysis of missing data, the analysis of missing values of the SPSS statistical package will be used. In most situations it is not possible to verify the association of the missing data with other variables that allow it to be used to impute them in a probabilistic way; the Little’s MCAR test will be used to determine if the missing data occurs completely randomly (“Missing Completely at Random Data: MCAR”) and if its imputation is necessary. If the value of p obtained is less than 0.5, it cannot be assumed that the data are completely lost by chance and a multiple imputation will be made.

The dependent variables of our study will be BMI, skinfold thickness of the triceps, waist/hip ratio (as anthropometric variables) and the prevalence of overweight and obesity. As surrogate or intermediate variables we will analyze behaviors related to eating, physical activity and sedentary lifestyle, hours of sleep, knowledge and beliefs about eating and physical activity, as well as the physical condition (IFIS) [44,45] of the children.

In the models, possible covariates related to personal, family, school and environment characteristics will be analyzed. Especially will be analyzed: sex, birth weight, breastfeeding, sociodemographic characteristics, family socioeconomic level, level of physical activity and time of sedentary activities of the parents; behavior, knowledge and beliefs about family food and physical activity, participation of the school in the intervention and level of adherence, participation of the center in other health promotion programs, availability or use of the school canteen and the existence of health assets in the environment.

To determine the efficacy of the different components of the intervention, predictive models will be obtained for each of the outcome variables by backward multiple linear regression, in which all possible components are included and are progressively eliminated from lowest to highest contribution. To analyze the specific contribution of a certain component on a dependent variable, the semi-partial correlations will be obtained; this method allows the effect of the component to be controlled to be subtracted from the predictors being treated. The R^2^ values of the components measure their theoretical contribution and allow establishing a theoretical hierarchy among the components that will be used in the regression by blocks; by changing R^2^ the different contributions of the variables will be seen.

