## 2. Materials and Methods

### 2.1. Study Design and Participants

The current study will have a quasi-experimental design with a control group, which will be target children enrolled in third grade of primary education from 26 schools of the province of Cádiz. The inclusion criteria that will be used will be: children belonging to the selected school, who are in the third grade of primary school, regardless of their age, who have the informed consent signed by their parents or legal guardians, who respond to the questionnaires and who undergo to the anthropometric measurements. The exclusion criteria will be that these requirements are not met.

The total number of study participants will be between 850 and 900 children. The parents of each schoolchild will be part of that same subject (father, mother and child are the same subject of study). The sample will be divided into two groups, the intervention group and the control group. The intervention group will contain around 450 schoolchildren and will be made up of 13 of the 26 school centers which will participate in the study. In this group, pre-intervention measurements will be performed, which will be explained later. A multimodal intervention will be developed, which will also be explained in detail later. Finally, post-intervention measurements will be made, which will be the same as the pre-intervention measurements. The control group will also contain around 450 schoolchildren and will be made up of the others 13 school centers which will participate in the study. It will be made up of the same number of schoolchildren. The difference with respect to the intervention group will be that the control group will not receive any educational intervention. Only the pre- and post-intervention measurements will be taken, to later compare the results with the intervention group and find out if an effect has emerged or not.

The province of Cádiz will be divided into four areas: Campo de Gibraltar (six schools), Jerez-Costa Noroeste (five schools), Sierra de Cádiz (nine schools) and Bahía de Cádiz-La Janda (six schools) (Figure 1). In each area, there will be between 200 and 300 participants and school centers belonging to both the intervention group and the control group. This division will be made to have a sample that is as representative as possible of the entire province of Cádiz.

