Both the selection of schools participating in the study and the assignment of them to the experimental group or control group will be made randomly from the list of public schools of the Cádiz Education Delegation. These randomizations will be carried out taking into account the schools belonging to each of the geographical areas in which the province of Cádiz will be divided, the socioeconomic condition of the population served, which will be determined from the Material Deprivation Index (MDI) of the section of the census in which the school is located [37], and the number of classes or corresponding lines of each center belonging to that age group. Randomization will be carried out in groups by schools, not individually. 

The group of schoolchildren will constitute the first level of analysis, and the schools will be the second level. This target population (children 8–9 years) has been selected due to the need to detect and solve the problem of childhood obesity in early stages to promote healthier lifestyle habits, and thus achieve health benefits that allow correct weight management from childhood until adulthood, and because, at this age, children are very receptive to receiving information that implies changes in habits [23].

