### 2.2. Calculation of the Sample Size

To determine the effectiveness of the intervention on the prevalence of overweight and obesity, the sample size necessary to test hypotheses has been calculated, comparing two proportions. We will compare the percentage of overweight and obesity of schoolchildren before and after the intervention in both groups (intervention and control) (paired data) and inter-group (independent data). In our case, for an estimated difference of proportions of 9% (35% vs. 26%) with a confidence level of 95% and a power of 80%, the minimum sample size required is 410 subjects in each group (intervention and control), which makes a total of 820 subjects. For the calculation of the sample, after reviewing the results obtained by different studies carried out in our environment, it has been assumed an estimated prevalence of overweight and obesity of a 35%, which was found by Villagrán et al. (2013) [9] in a population of Cádiz similar to that of this study.

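### The effectiveness contrast compares changes, and the covariate list names neither the child's baseline value and age nor the school's deprivation index and number of lines; adjusting for them costs nothing

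*Protocol article*

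**What the plan says.** On how effectiveness is judged, Section 2.5 of the protocol article says: "The effectiveness will be studied by comparing the changes in the groups". The sentence before it lists chi-square, t-test and ANOVA for comparing percentages and means. The sentences after it plan simple and multiple linear or logistic regression, a grouping term for intraclass correlation, and a multilevel analysis whose levels include geographical area and school with line or classroom. A longitudinal analysis by MANOVA or generalised linear models follows. None of these is named as the source of the main effectiveness estimate.

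The same section then gives covariates for the models. It opens with broad classes (personal, family, school and environment) and continues: "Especially will be analyzed: sex, birth weight, breastfeeding, sociodemographic characteristics, family socioeconomic level". The list goes on to parental activity, knowledge and beliefs, adherence, other health promotion programmes, canteen use and health assets. Baseline BMI or weight status, age, the Material Deprivation Index and the number of lines are not named.

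Section 2.1 says schools are selected and allocated at random, taking account of geographical area, the Material Deprivation Index of the school's census section, and "the number of classes or corresponding lines of each center belonging to that age group". Children enter by school grade, whatever their age.

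Section 2.2 adds a paired comparison beside the between-group one: "We will compare the percentage of overweight and obesity of schoolchildren before and after the intervention in both groups".

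**The concern.** The baseline measurement is usually the strongest predictor of the follow-up measurement, and this trial takes it on every child. A change score uses it, but with the slope on baseline fixed at 1. If the true slope is below 1, two things follow. Some precision is lost. And if one arm starts heavier by chance, that arm is expected to show a larger fall through regression to the mean, which the change score counts as an effect. With 13 schools per arm, a chance imbalance of this kind is realistic.

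Factors used in allocation normally belong in the analysis, and two of the three are not named there. Age matters because raw BMI is a dependent variable and age is not an entry criterion. Before-after comparisons within an arm mix any intervention effect with growth and season over at least six months, so they cannot by themselves show effectiveness.

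**Working it through.** **1. The plan's own figure.** Inputs from Section 2.2: 35% against 26%, 95% confidence (two-sided assumed), 80% power. With pooled variance and no continuity correction, n = [1.960·√(2·0.305·0.695) + 0.842·√(0.35·0.65 + 0.26·0.74)]² / 0.09² = (1.276 + 0.545)² / 0.0081 ≈ 410 per group. This reproduces the stated result ("the minimum sample size required is 410 subjects in each group (intervention and control), which makes a total of 820 subjects"). The calculation compares two independent proportions and uses no baseline information.

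**2. Continuous outcomes, by formula.** Let r be the pre-post correlation, which the article does not give, with equal standard deviations and clustering ignored. Variance relative to a follow-up-only comparison:
- change score: 2(1 − r)
- baseline-adjusted: 1 − r²
- ratio, adjusted to change: (1 + r)/2, so the standard error falls by 1 − √((1 + r)/2)

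| r (assumed) | Variance ratio | Fall in standard error |
|---|---|---|
| 0.5 | 0.75 | 13.4% |
| 0.7 | 0.85 | 7.8% |
| 0.8 | 0.90 | 5.1% |
| 0.9 | 0.95 | 2.5% |
| 0.95 | 0.975 | 1.3% |

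**3. Prevalence, by simulation.** The trial is sized on a dichotomised outcome. Weight status correlates over time less than BMI does, and baseline BMI carries information that baseline status lacks, so the formula in step 2 does not carry over. Inputs: 13 schools per arm (Section 2.1), about 34 children per school (roughly 450/13), 35% against 26% (Section 2.2). Assumed: intraclass correlation 0.02 and pre-post BMI correlation 0.8 to 0.95. There were 1,500 simulated trials per setting.

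| Outcome and adjustment | Correlation | SE, change score | SE, adjusted | Fall |
|---|---|---|---|---|
| Prevalence, baseline BMI plus status | 0.8 | 0.0308 | 0.0258 | 1 − 0.0258/0.0308 = 16% |
| Prevalence, baseline BMI plus status | 0.9 | 0.0259 | 0.0226 | 1 − 0.0226/0.0259 = 13% |
| Continuous BMI, own baseline | 0.9 | 0.0377 | 0.0364 | 1 − 0.0364/0.0377 = 3% |

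Over 0.8 to 0.95 the fall is about 11-16% for prevalence with baseline BMI and status, 5-10% for prevalence with baseline status only, and about 2-4% for continuous BMI. The last range agrees with step 2 to within simulation error.

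**4. Chance imbalance.** If the arms differ at baseline by Δ and the slope on baseline is r, a change score carries an expected error of (r − 1)Δ. That is −0.2Δ at r = 0.8 and −0.1Δ at r = 0.9. Baseline adjustment removes it. Averaged over random allocations Δ is zero, so this is an error given the imbalance that occurred, not a systematic bias.

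**5. Allocation factors against the analysis (Section 2.1 against 2.5).** Area is used in allocation and is a level of the multilevel model. The deprivation index and the number of lines are used in allocation and are not named in the analysis.

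**The case against.** The best defence is that the analysis is not unadjusted, and that is correct. The sentence on changes is followed at once by multiple regression, a grouping term and a multilevel model, and the covariate classes are broad. Several stronger readings are therefore tempting but not supported:

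- **That effectiveness rests on unadjusted tests.** The article lists chi-square, t-test and ANOVA just before that sentence, but does not say that changes are compared by those tests alone.
- **That the allocation factors are ignored.** Area is a level of the model, and line or classroom is a grouping unit. Only the deprivation index and the number of lines are missing by name. No calculation here shows that omitting them misstates the standard error.
- **That age is excluded.** It could fall under personal or sociodemographic characteristics. Section 2.4.3 uses age for BMI percentiles, and a within-child change removes stable age differences. Age is simply not committed to.
- **That before-after tests decide effectiveness.** In Section 2.2 they stand beside a between-group comparison.
- **That change scores are biased, or that the gain is large throughout.** Under the random allocation in Section 2.1 they are unbiased. Measuring the gain against a follow-up-only comparison would exaggerate it, since that is not the stated effectiveness contrast.

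It can also be said that exact covariate sets are often left to the analysis plan, which is not shown. That keeps the point modest. It does not remove it, because the article prints both a contrast and a long covariate list, and a better contrast is available from the same data.

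**Conclusion.** The point holds as a free improvement, not as an error that invalidates the analysis. The stated contrast compares changes; no sentence makes a baseline-adjusted model the main estimate; and four useful adjustment variables are not named, two of them used in allocation. Against change scores, adjustment lowers the standard error by about 11-16% for the prevalence difference, provided that both baseline BMI and weight status are used. For continuous BMI it lowers it by about 2-4%.

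These sizes rest on an intraclass correlation of 0.02 and pre-post correlations of 0.8 to 0.95, none of which the article gives. By the formula, the gain for a continuous outcome grows if its correlation is lower. Protection against chance baseline imbalance is the second benefit. No size is claimed for adjusting for age, deprivation index or lines, which the simulation did not include.

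**What to change.** In Section 2.5, replace the sentence on comparing changes with a named main analysis. The effectiveness estimate is the between-arm difference in the post-intervention outcome, from the school-level mixed model already planned. It is adjusted for:
- the child's baseline value of that outcome (for prevalence, both baseline BMI and baseline weight status)
- age at measurement and sex
- geographical area, the school's Material Deprivation Index and its number of lines

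In Section 2.2, say that before-after changes within each arm will be described, and will not be taken as evidence of effectiveness.

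Cost: wording only. Baseline anthropometry is measured under Section 2.4.3, age is needed there for the percentiles, sex is already a listed covariate, and area, index and lines are held for the allocation. No extra children, visits or questionnaires are needed. The school-level terms do use degrees of freedom: with area as a four-category factor (3), index (1), lines (1), arm (1) and intercept (1), 26 − 7 = 19 remain between schools. This is workable, but a small-sample correction should be stated.

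### Section 2.5 lists the intervention arm as a level of grouping, in conflict with Section 2.1; arm should be stated as a school-level fixed effect tested against between-school variation

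*Protocol article*

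**What the plan says.** Protocol article, Section 2.1 (Study Design and Participants):
- The unit of allocation is the school: "Randomization will be carried out in groups by schools, not individually".
- The intervention group "will be made up of 13 of the 26 school centers which will participate in the study"; the other 13 schools form the control group.
- The level structure has two tiers: "The group of schoolchildren will constitute the first level of analysis, and the schools will be the second level".

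Protocol article, Section 2.5 (Statistical Analysis):
- The intent is to allow for clustering: "The grouping term will be modeled in the analysis to adjust the effect of the intraclass correlation and a multilevel test will be conducted".
- The structure is then a list of four. It starts with area, goes on to municipality, and next combines school with classroom on one tier. Arm closes the list after those three: "the fourth and last will be given by the intervention (control and experimental group".
- For longitudinal data, "MANOVA of maximum likelihood and least squares will be used under conditions of normality of the data", with generalized linear models if normality fails. No school term is attached to either.
- Effectiveness is to be judged by comparing changes between the groups.

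**The concern.** Arm is the allocated exposure whose effect the study is meant to estimate. A level of grouping is a set of units whose variation is allowed for. Putting arm in the second role leaves unclear how the effect is to be estimated and against which error. With allocation by school, the relevant error is the variation between schools within an arm.

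The two sections also disagree. Section 2.1 has two levels and Section 2.5 has four. Section 2.5 adds area, municipality and arm, and merges the school, which is the allocated unit, with the classroom. An analyst cannot tell which structure applies. At stake is the standard error of the main comparison.

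**Working it through.** The plan gives no figure for this point, so the check is mainly structural. The one related figure is the sample size in Section 2.2, which reproduces. For 35% vs 26%, two-sided 5% and 80% power, with pooled proportion 0.305:

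n = [1.960·√(2·0.305·0.695) + 0.842·√(0.35·0.65 + 0.26·0.74)]² / 0.09² = 409.6, so 410 per group.

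It shows only that the planned numbers are on the child scale. Whether they suffice under clustering is a separate matter.

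**1. The two level structures side by side**

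| | Section 2.1 | Section 2.5 |
|---|---|---|
| Number of levels | 2 | 4 |
| Child | level 1 | not listed |
| School | level 2 | level 3, merged with classroom |
| Area, municipality | not levels | levels 1 and 2 |
| Arm | not a level | level 4 |

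Numbering from the top down rather than from the bottom up explains the order. It does not explain the presence of arm or the merging of school with classroom.

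**2. Arm as a level nested under school**

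Inputs: 26 schools, 13 per arm, one arm per school. Let S be the 26 × 26 indicator matrix for schools, and let A be the indicator matrix for arm within school. Of the 52 possible school-by-arm cells, only 26 are occupied, so A also has 26 columns.
- Rank of S = 26; rank of [S, A] = 26.
- SSᵀ = AAᵀ, so the two terms imply the same covariance pattern.

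An arm level under school is therefore fully aliased with school and adds nothing. Arm is equally constant within each classroom, so the same holds one step lower.

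**3. Arm as a separate grouping factor**

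It has two units. A grouping factor of this kind gives a variance estimated from two units, not a difference between arms with a confidence interval.

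Under neither literal reading is the arm difference set against between-school variation.

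**4. Conditional illustration: what happens if the school term is left out**

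Inputs: 450 children / 13 schools = 34.6 per school (Section 2.1). The intraclass correlation (ICC) is not given and is assumed to be 0.01 to 0.05.

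Design effect DE = 1 + (34.6 − 1)·ICC. True type I error = 2·[1 − Φ(1.96/√DE)].

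| Assumed ICC | DE | True error of a nominal 5% test |
|---|---|---|
| 0.01 | 1.34 | 9.0% |
| 0.02 | 1.67 | 13.0% |
| 0.05 | 2.68 | 23.1% |

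A simulation under no effect (20,000 runs, 13 schools per arm, 33 children per school, prevalence 35%) gave 9.0%, 12.8% and 22.5% at the same ICCs for a child-level test. A school-level t-test stayed between 4.8% and 5.3% over ICCs of 0.01 to 0.05.

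**The case against.** The strongest reply is that the plan handles clustering and the list is only loosely worded. Section 2.5 commits to modelling the grouping term for the intraclass correlation and names the school among the levels. It promises odds ratios with 95% confidence intervals. Among its possible covariates it names the school's taking part in the intervention, paired with the level of adherence, which may be arm under another name. Section 2.5 says neither that the levels are random nor that arm is nested; both are inferred from the word for grouping and from the order of the list. A child is also a unit rather than a grouping, so leaving it off a list of groupings is no great fault.

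Much of this stands, and it rules out some stronger readings that a reader might infer:
- *That the plan cannot produce an effect estimate with valid error.* The regression, covariate and clustering statements leave room for a sound analysis. The fault is in the listed structure.
- *That the intervention would be tested on one degree of freedom.* Two units would leave 1 df, but no such test is planned.
- *That the planned tests have 9% to 23% type I error.* That would require dropping the school term which the plan says it will model. The chi-square and t-tests follow directly on the descriptive analysis and are not named as primary.
- *That the MANOVA ignores schools.* The text does not say so. It simply does not say how that analysis and the multilevel one fit together.

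What does not stand is that this is detail left to a fuller document. The article states a structure, and that structure is wrong as stated. The covariate does not rescue it: it is listed only as possible, it may refer to implementation, and if it is arm, then arm enters the model twice.

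**Conclusion.** The point holds as a mis-stated model that should be fixed. Arm is constant within school, so it does not belong among the levels of grouping, and the four-level list conflicts with the two-level structure of Section 2.1. Taken literally, the list does not test the intervention against between-school variation. This rests only on allocation by whole schools and 13 schools per arm, both stated.

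The intent to adjust for intraclass correlation is clear and the design itself is unaffected, which is why the point is not graded higher. The error rates of about 9%, 13% and 23% rest on assumed ICCs, about 35 children per school, and omission of the school term. They show why the wording matters and are not a property of the plan as written.

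**What to change.** In Section 2.5:
- Take arm off the list of grouping levels and state it as a school-level fixed effect. Since effectiveness is judged on change, use either arm adjusted for the baseline value or arm by time. In the arm-by-time form, the school effect must also apply to the change over time.
- Put children at level 1 and make school the random clustering unit, with classroom within school if needed.
- Enter area as a fixed stratum. It has four categories and was taken into account in the allocation.
- Base inference on the 26 schools.
- State that any longitudinal MANOVA or generalized linear model used for the arm comparison also carries the school effect, or is replaced by this model.

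Then bring the level description in Section 2.1 into line. The choice of small-sample correction and the handling of municipality can be left to the analysis plan.

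The cost is wording in two sections, with no change to design, data collection or sample. Intervals will be wider than those from an analysis that ignored school, as they should be.
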